**3.2 Secondary Aims**

- Secondary objectives are to assess, in this population of vitamin D deficient individuals at high risk of type 2 diabetes, the effect of treatment on:
  1. Inflammatory markers;
  2. Adiponectin and osteocalcin;
  3. Insulin resistance using the revised Quicki index;
  4. Blood pressure;
  5. Lipid profile;
  6. Fasting free-fatty acid (FFA) levels;
  7. Body weight.
- We also seek to determine whether vitamin D requirements (to achieve a level of 25OHD ≥75 nmol/L) are influenced by fat mass (dual X-ray absorptiometry - DXA) in this population of overweight individuals.

**5. Project Design**

**5.1 Study Population/Recruitment strategies**

Eighty (80) overweight or obese, vitamin D deficient and glucose intolerant subjects with various ethnic backgrounds will be enrolled in this study. Most participants will be recruited from local General Practices. Recruitment via the GP clinics will be done in two phases.

- First phase: The Diabetes Risk Score questionnaire, a simple tool developed from large epidemiological studies, will be used to maximize the yield of finding glucose intolerant subjects. In one recently published study, about a third of the individuals with a screening score of 12 or more turned out to be glucose intolerants [51]. This cut-off will therefore be used to identify patients for OGTT testing. This simple self-administered questionnaire as well as an invitation to participate in the study will be given by the GPs secretary when the patient registers for his appointment. If the patient agrees to be contacted (by giving his contact details), he will give this letter back to the secretary that will send it to the research team. The research team of Western hospital will then contact the patient to make an appointment (to explain the protocol, sign the consent form and proceed with the screening OGTT). Advertisements will also be put on the walls of the clinics waiting room.
- Phase 2 (this strategy will be only applied if the phase 1 recruitment strategies have failed. A separate consent form will be used for this recruitment strategy): After presenting the project to GP groups and obtained their agreement, a nurse or the study investigators will screen patients in the clinic waiting room. While patients will be waiting for their appointment with their GP, the researchers ([name]) or the research assistant will ask if they would like to participate in the study. If they agree, they will be transferred in a private room to read the consent form and sign it. They will then have their weight, height and waist circumference. These measurements will be used to answer the Diabetes Risk Score questionnaire. If the score of the patient is 12 or more, he (she) will be given an appointment for an OGTT. The researchers and the GPs will receive the results of this test and contact the patient if he (she) is eligible to participate in this study. Of note, by signing this version of the consent form (only for recruitment of participants from GP clinics – Phase 2), the patient accepts that the researchers and the GPs receive a copy of the OGTT results, access their medical record and contact them if they are eligible to participate in the study. The subsequent visits will be held at Western Hospital.

Participants will also be recruited from outpatient clinics in Western Health (Sunshine, Footscray and Williamstown campuses) and Royal Melbourne Hospital (RMH). More specifically, patients who are on the waiting list for obesity clinic at RMH and Western hospital will be invited by mail to participate in this study. In addition, patients who had gestational diabetes and attended the gestational diabetes clinic in the last 5 years will also receive an invitation. Finally, announcements will be made in local newspapers, radio and also displayed in the above mentioned hospitals, in strategic locations planned for this purpose.

**5.2 Randomisation and Intervention**

The proposed study is a prospective, double blind, randomised and placebo controlled 6-month clinical trial. Subjects will be randomly assigned to one of two groups, with stratification according to sex, age (< or >50 years of age) and BMI (< or >30). The treatment group will receive vitamin D_3_ (cholecalciferol) 2000 IU plus calcium carbonate (1200 mg elemental Ca daily) and the control group will take placebo pills. Permuted blocks of 4 treatment allocations will be used to ensure that after each 4^th^ allocation there are equal numbers in each treatment arm. After 8 weeks of treatment, if subjects in the treatment group have 25OHD levels less than 75 nmol/L, the dose of cholecalciferol will be increased to 4000 IU daily to reach optimal levels. On the other hand, subjects in the placebo group and those in the treatment group that reached optimal levels of 25OHD will be given extra placebo pills. To ensure blinding is respected, a person external to the study will look at the 8-week 25OHD results and contact patients to add an extra cholecalciferol or placebo pill to their regime, as appropriate.

The dosage of cholecalciferol has been estimated from the study of Barger-Lux and al., a rigorous trial performed in healthy overweight men [52]. They showed that each mcg (40 IU) of vitamin D_3_ increase the 25OHD concentration by 0.70 nmol/L. Based on the mean 25OHD level reported in populations of obese vitamin D deficient subjects (30 nmol/L) [25, 50, 53] and the expected increment described previously, it can be estimated that 2400 IU daily of vitamin D_3_ would be needed to increase the mean 25OHD level of our population to over 75 nmol/L. Of note, the dose-response relationship was not affected by body weight or fat mass. However, other data suggest that vitamin D requirements might be higher in obese compared to normal weight subjects [54]. Therefore, given that participants in our study will be obese, if adequate 25OHD levels are not reached after 8 weeks, the dose of cholecalciferol will be increased to 4000 IU daily. This dose, given daily for 3 months to 28 healthy adults, increased mean 25OHD levels from 37.9 ± 13.4 nmol/L to 96.4 ± 14.6 nmol/L [55]. None of the subjects had 25OHD levels <75 nmol/L at the end of the study.

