**5.6 Statistical analyses**

Analyses will be performed using SPSS version 15.0. Skewed data will be log-transformed or examined using non-parametric tests. Differences in delta HOMA-IR between the treatment and the placebo group will be compared by two-sample unpaired *t* test. The change in DI and in ISR (assessed by deconvolution analysis of C-peptide levels and the insulinogenic index) and also the total area under the curve of C-peptide by deconvolution analysis will be compared between groups with unpaired *t* test. Analyses will be performed to assess changes in inflammatory markers, intact osteocalcin, adiponectin, blood pressure, lipid profile, FFA and weight with a two-sample unpaired *t* test. A *P*-value of ≤0.05 will be considered statistically significant. The endpoints will be adjusted for risk factors of type 2 diabetes: age, sex, BMI, family history of type 2 diabetes and physical activity. The following covariates will also be adjusted for: sunlight exposure and VD and calcium intake. Finally, the variables that predict response to treatment will be identified with multiple linear regression analyses. We will perform data analysis on an intention-to-treat principle. We will also perform analysis on patients who achieved >75% compliance with study medication as well as those on active treatment who achieved target 25OHD levels ≥75 nmol/L.

*Sample size calculation*

Sample size calculation is based on the difference in delta HOMA-IR [0.15 ± 0.18 (SD)] observed in a similar population of overweight subjects with pre-diabetes before and after a mean weight loss of 9.8 kg [64]. This change in HOMA-IR resulted in improved beta-cell function and reduction in the area under glucose curve during OGTT. This change in HOMA-IR was therefore considered clinically significant and was chosen for sample size calculation. A sample of 32 participants in each group will have 90% power to detect a difference in delta HOMA-IR of 0.15 with a standard deviation of 0.18 and 2-sided alpha of 0.05. Assuming a drop out rate of 20%, we will study a total of 80 participants.

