**5.8 Potential sources of bias**

The main factors that could affect insulin sensitivity, and consequently, insulin secretion are physical activity and weight change. Physical activity will be evaluated with questionnaires at the beginning and at the end of the study. This factor will be taken into account in the analyses. However, some data suggest that calcium supplementation could induce weight loss [65, 66]. If significant weight loss is observed between the treatment and placebo group, it will be difficult to discriminate the beneficial effects of calcium and vitamin D on insulin sensitivity and secretion from those induced by weight loss. However, this will be adjusted for in multivariate analysis.

Seasonal variation can influence endogenous 25OHD production. With small number block randomisation, this effect will be minimised by distributing patients equally between treatment groups within a small time frame.

1. Dunstan, D.W., et al., *The rising prevalence of diabetes and impaired glucose tolerance: the Australian Diabetes, Obesity and Lifestyle Study.* Diabetes Care, 2002. **25**(5): p. 829-34.
2. Cameron, A.J., et al., *Overweight and obesity in Australia: the 1999-2000 Australian Diabetes, Obesity and Lifestyle Study (AusDiab).* Med J Aust, 2003. **178**(9): p. 427-32.
3. Giulietti, A., et al., *Monocytes from type 2 diabetic patients have a pro-inflammatory profile. 1,25-Dihydroxyvitamin D(3) works as anti-inflammatory.* Diabetes Res Clin Pract, 2007. **77**(1): p. 47-57.
4. Targher, G., et al., *Serum 25-hydroxyvitamin D3 concentrations and carotid artery intima-media thickness among type 2 diabetic patients.* Clin Endocrinol (Oxf), 2006. **65**(5): p. 593-7.
5. Cigolini, M., et al., *Serum 25-hydroxyvitamin D3 concentrations and prevalence of cardiovascular disease among type 2 diabetic patients.* Diabetes Care, 2006. **29**(3): p. 722-4.
6. Li, Y.C., et al., *1,25-Dihydroxyvitamin D(3) is a negative endocrine regulator of the renin-angiotensin system.* J Clin Invest, 2002. **110**(2): p. 229-38.
7. Billaudel, B., L. Barakat, and A. Faure-Dussert, *Vitamin D3 deficiency and alterations of glucose metabolism in rat endocrine pancreas.* Diabetes Metab, 1998. **24**(4): p. 344-50.
8. Tanaka, Y., et al., *Effect of vitamin D3 on the pancreatic secretion of insulin and somatostatin.* Acta Endocrinol (Copenh), 1984. **105**(4): p. 528-33.

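### Section 5.8 relies on small blocks to balance the arms within short periods, but blocks of 4 within 8 strata balance them only within each stratum

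*Protocol*

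**What the plan says.** Protocol 5.2 assigns participants to two groups, stratified by three two-level factors: sex, age either side of 50, and BMI either side of 30. It continues: "Permuted blocks of 4 treatment allocations will be used", so that "after each 4^th^ allocation there are equal numbers in each treatment arm". It does not say whether the blocks run within strata or on one common list, nor whether the 4th allocation is counted within a stratum or across the trial.

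Protocol 5.8 names season as a possible source of bias through endogenous 25OHD production, and answers it with the block design: "With small number block randomisation, this effect will be minimised by distributing patients equally between treatment groups within a small time frame".

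Protocol 5.6 compares the change in HOMA-IR by an unpaired t test and also provides for adjustment. The covariates listed are age, sex, BMI, family history of type 2 diabetes, physical activity, sunlight exposure, and vitamin D and calcium intake. Season or date of randomisation is not among them. On numbers, "we will study a total of 80 participants".

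**The concern.** The argument in 5.8 needs the two arms to be equal across the whole trial over short stretches of calendar time. One unstratified list with blocks of 4 would give that, but would not deliver the stratification in 5.2. Separate lists in 8 cells deliver the stratification, but up to 8 blocks are then open at once and consecutive enrolments need not be balanced. The two sections cannot both hold as written.

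Season matters here on the protocol's own account. Section 1.2 cites worse glycaemic control at the end of winter, and 5.8 lists season under bias. The endpoint is a 6-month change, so the first and last visits fall half a year apart and the date of entry may bear on the outcome. Blocking is the only safeguard that 5.8 names for season. If it is weaker than described, some chance seasonal imbalance remains, and readers are given too favourable a description of the design.

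**Working it through.** **Inputs.** From 5.2: three binary stratification factors, two arms, block size 4. From 5.6: 80 participants. Assumed, because the protocol gives no recruitment duration: a season corresponds to 20 consecutive enrolments, a quarter of recruitment. Also assumed: the mix of participants across strata, which is varied below.

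**The plan's own figure.** For a difference of 0.15, SD 0.18 and two-sided alpha 0.05, the noncentral t gives 89.8% power at 31 per group and 90.7% at 32. Then 64 / (1 - 0.20) = 80. The sample size reproduces and is not in dispute; it only supplies N.

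**Cells and block span.** 2 x 2 x 2 = 8 cells, and 80 / 8 = 10 participants per cell if cells are equal. A block uses 4 of those 10, or 40% of recruitment. Counted from the first to the last member of a block, it is three gaps of about 8 enrolments: 3 x 8 = 24, and 24 / 80 = 30%. Larger cells fill faster and smaller ones slower.

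**Analytic check of overall imbalance.** Within a block the arm difference has variance 1, 4/3, 1 and 0 after 1, 2, 3 and 4 allocations, with mean (1 + 4/3 + 1 + 0) / 4 = 0.83. Over 8 cells, 8 x 0.83 = 6.7, so the SD is 2.6. The simulated SD at the end of the trial is also 2.6. The largest possible cumulative difference is 8 x 2 = 16.

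**Simulation.** Permuted blocks of 4 on one list or within 8 cells, and simple randomisation, each with N = 80. The main runs used 20,000 trials.

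| Scheme | Arms equal at trial-wide 4th allocations | 20-patient window: differ by 4 or more | by 6 or more | SD of window difference |
|---|---|---|---|---|
| One unstratified list | 100% | 0% | 0% | 0 |
| 8 equal cells | 31% | 33% | 11% | 3.2 |
| 8 uneven cells (two mixes) | 32-33% | 27-31% | 7-9% | 2.8-3.0 |
| Simple randomisation | 15% | 50% | 26% | 4.5 |

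Further runs put 80% or 90% of participants in one BMI stratum (sex 60/40 and age 50/50 assumed). They give 29% and 8%, and 25% and 6%, for differences of 4 or more and 6 or more. Across all mixes the ranges are therefore about 25-33% and 6-11%. In none of the 20,000 equal-cell trials were the arms equal at every trial-wide 4th allocation.

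**Possible effect on the estimate.** Suppose, with no source in the protocol, that one season shifts delta HOMA-IR by 0.15. A 13 v 7 split in that season with 40 per arm moves the estimate by (13 - 7) / 40 x 0.15 = 0.0225, which is 15% of the target difference. The standard error is 0.18 x sqrt(2/40) = 0.040, so the shift is about 0.56 of a standard error. At one SD of the window difference, the shift is 3.2 / 40 x 0.15 = 0.012, or about 0.3 of a standard error.

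**The case against.** The strongest reply is that the balance sentence in 5.2 is true on its ordinary reading. Stratification is announced just before it, blocks in a stratified scheme normally run within strata, and the arms are then equal after each 4th allocation in a stratum. That stands. A reader might infer from the 31% figure that 5.2 makes a false statement; the text does not support this, because 5.2 never says the count is trial-wide. The difficulty lies in 5.8, which needs the trial-wide property.

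Section 5.8 also says only that the seasonal effect is minimised. A reader might infer that balance over time is promised outright, but the protocol does not go so far. The direction of its claim is right, since stratified blocks do better than simple randomisation. What fails is the reason given, equal distribution within a small time frame.

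A reader might further infer that a seasonal imbalance would go wholly unadjusted. It would not: 5.6 already adjusts for sunlight exposure, which bears directly on the 25OHD route that 5.8 names, and for physical activity, age, sex and BMI. Section 5.5 collects the sunlight and activity questionnaires at baseline and at the end. Self-reported sunlight is still only a partial stand-in for season.

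Finally, the 20-patient window and the seasonal shift of 0.15 are assumptions, and the shift is as large as the whole target difference. That also stands, and it keeps the likely consequence small.

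**Conclusion.** The point holds as an overstated design property. With the stratification in 5.2, blocks of 4 do not distribute participants equally between arms within short periods, so 5.8 credits blocking with more control of season than it gives. The structural conclusion needs only the 8 cells and the block size. The window percentages also rest on the assumed 20-patient season and stratum mix.

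It would be wrong to read this as systematic bias. Randomisation balances season in expectation, and chance imbalance is already covered by the error rate of the test. Unequal arm sizes have a negligible effect on power. Under a seasonal shift as large as the target difference, an unfavourable split moves the estimate by about half a standard error, and a smaller shift moves it proportionally less. The change is worth making because it is cheap and the protocol itself names the confounder.

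**What to change.** - **5.2:** state that blocks of 4 run within each of the 8 strata and balance the arms there.
- **5.8:** say that stratified blocking reduces seasonal imbalance compared with simple randomisation but does not ensure equal arms over short periods.
- **5.6:** add season of randomisation to the covariates of the adjusted analysis, for example warm v cool half-year, or sine and cosine of the date. It would sit beside the sunlight exposure, age, sex and BMI already listed, so the stratification factors need no new terms.

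The cost is some wording and one or two degrees of freedom. The randomisation date is known, so no new data are needed. The season term will overlap to some extent with the sunlight questionnaire.

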**5.3 Inclusion Criteria**

1. Age ≥ 18 years;
2. Any ethnicity;
3. Vitamin D deficiency documented by a serum 25OHD concentration ≤ 50 nmol/L;
4. Overweight or obesity (BMI ≥ 25 kg/m^2^ and ≤ 40 kg/m^2^);
5. Glucose intolerance confirmed with a 75g OGTT in the last 3 months: fasting plasma glucose < 7.0 mmol/L and/or 2h post glucose load between 7.8 and 11.0 mmol/L (WHO criteria 1999);
6. Ability to give an informed consent.

**5.4 Exclusion Criteria**

1. Pregnancy or intention to become pregnant in the next 6 months;
2. Breast-feeding;
3. Renal insufficiency (creatinine clearance < 60 ml/minute);
4. Cirrhosis;
5. Malabsorption*;
6. Known history of hypercalcemia, hypercalciuria or nephrolithiasis;
7. Previous fractures;
8. Known active inflammatory disease;
9. Medications known to affect vitamin D, calcium or bone metabolism, such as vitamin D and calcium supplements, bisphosphonates, glucocorticoids, thiazide diuretics, anticonvulsivants and lithium over the last 3 months;
10. Pharmacological treatment for obesity or medications known to alter glucose metabolism over the last 3 months;
11. Bariatric surgery planned in the next six months or patients who had undergone bariatric surgery in the past;
12. More than 5% change in weight in the last 3 months;
13. Current smoking.

* Every participant will be screened for celiac disease (anti-tissue transglutaminase antibodies). Those with positive results will be excluded from the study and referred to their family physician for further investigation and treatment.

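### The exclusions for vitamin D/calcium drugs and for obesity/glucose drugs look back 3 months but not forward, so people who already plan to start these treatments during the 6-month trial are eligible

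*Protocol*

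**What the plan says.** The exclusion criteria in Protocol section 5.4 use two kinds of time window.

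- **Backward only, 3 months.** Criterion 9 covers "Medications known to affect vitamin D, calcium or bone metabolism, such as vitamin D and calcium supplements" and other listed drugs, and ends with a 3-month look-back. Criterion 10 covers "Pharmacological treatment for obesity or medications known to alter glucose metabolism over the last 3 months". Criterion 12 covers "More than 5% change in weight in the last 3 months".
- **Forward, 6 months.** Criterion 1 covers intended pregnancy. Criterion 11 covers "Bariatric surgery planned in the next six months or patients who had undergone bariatric surgery in the past".

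Treatment lasts 6 months (5.2). Most participants come from general practices, but 5.1 adds that "patients who are on the waiting list for obesity clinic at RMH and Western hospital will be invited by mail to participate in this study". Every participant has 25OHD of 50 nmol/L or less (5.3, criterion 3).

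After entry, participants report medication changes. Weight is measured at baseline, 2 months and the end, and vitamin D and calcium intake is estimated by questionnaire at baseline and the end (5.5). Serum 25OHD is monitored at 2 and 6 months (5.5). Section 5.6 adjusts for BMI, physical activity, and vitamin D and calcium intake. No section bars starting vitamin D, obesity drugs, glucose-altering drugs or a weight-loss programme during the trial.

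**The concern.** The trial treats planned weight-loss surgery as a reason for exclusion, but not planned drug or programme treatment for the same condition. It also invites people who are waiting for an obesity clinic. Someone who has taken none of the listed drugs in the past 3 months, but already intends to start one, meets every criterion.

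The protocol's own text shows why this matters. Section 5.8 states: "The main factors that could affect insulin sensitivity, and consequently, insulin secretion are physical activity and weight change". The target effect in 5.6, a HOMA-IR change of 0.15, was observed "before and after a mean weight loss of 9.8 kg". A weight-loss treatment begun during follow-up could therefore move one participant's HOMA-IR by as much as the whole effect sought, in either arm. A placebo participant who starts vitamin D receives part of the study intervention, which shrinks the difference between arms.

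**Working it through.** **Inputs.** From 5.6: difference 0.15, SD 0.18, 32 per arm, two-sided alpha 0.05, unpaired t test, 20% drop-out. The share *p* who start a treatment is an assumption, because the protocol gives no rate.

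**The plan's own figure.** Noncentral t with 62 degrees of freedom and noncentrality 0.15 / (0.18 × √(2/32)) = 0.15 / 0.045 = 3.33 gives power 90.7%. The smallest n per arm reaching 90% is 32, and 64 / 0.8 = 80. The stated sample size reproduces. The reserve above 90% is under one point.

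**A. Weight-loss treatment started equally in both arms, each starter shifting by the full 0.15.** The expected difference stays 0.15. The SD becomes √(0.18² + p(1−p) × 0.15²).

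| p | SD | Power at 32 per arm |
|---|---|---|
| 10% | 0.186 | 88.9% |
| 20% | 0.190 | 87.6% |
| 30% | 0.193 | 86.6% |

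This is a loss of about 2 to 4 points, through variance alone. Chance imbalance in the number of starters is not an additional harm. At p = 20% it has a 95% range of 1.96 × 0.15 × √(2 × 0.2 × 0.8 / 32) = 0.029. The half-width for the difference goes from 1.96 × 0.18 × √(2/32) = 0.088 to 1.96 × 0.190 × √(2/32) = 0.093, and √(0.088² + 0.029²) = 0.093. It is the same variance.

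**B. Vitamin D started by a share p of the placebo arm only.** If each starter gains *g*, the expected difference is 0.15 − p × g. The placebo variance becomes 0.18² + p(1−p) × g², and the SD used is the root mean of the two arms' variances.

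| Gain per starter | p | Difference | Power (with added variance) | Power (SD held at 0.18) |
|---|---|---|---|---|
| Full, 0.15 | 10% | 0.135 | 82.8% | 84.0% |
| Full, 0.15 | 20% | 0.120 | 72.4% | 74.7% |
| Half, 0.075 | 10% | 0.1425 | 87.4% | 87.6% |
| Half, 0.075 | 20% | 0.135 | 83.5% | 84.0% |

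The full-gain rows are an upper bound on the harm. They credit a participant who takes vitamin D alone with the whole effect of vitamin D plus calcium, whereas the rationale in section 2 expects the two effects to be additive.

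**The case against.** The strongest case against the point is as follows.

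- **The protocol has safeguards.** Weight at three visits, 25OHD at 2 and 6 months, intake and activity questionnaires, medication reports and covariate adjustment would all help to reveal or account for such starts. This stands in part. These measures detect starts but do not prevent them. Adjusting for weight change after randomisation may also remove part of a treatment effect, since 5.8 itself notes that calcium might cause weight loss.
- **The waiting-list route costs little.** This stands. Starts that are equal across randomised, blinded arms add variance and do not bias the contrast, and most participants come from general practices. The larger losses in B come from vitamin D in the placebo arm, which has no particular link to the waiting lists.
- **No start rate and no waiting time are given.** This stands. A wait longer than 6 months is as compatible with the text as a short one. Under the phase 2 recruitment route the GP receives the OGTT result, not the 25OHD result, so that route does not in itself prompt vitamin D.
- **How post-entry starts are analysed can be left to the SAP.** This stands for the analysis, but not for the eligibility wording, which belongs in the protocol.

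A reader might infer that the contrast *will* be blurred, or that 5.8 concedes that outside weight-loss treatment cannot be untangled. Neither is supported. The first needs a rate that the protocol does not give. The difficulty described in 5.8 concerns weight loss possibly induced by the study calcium, and the next sentence there proposes adjustment.

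**Conclusion.** The point holds as an inconsistency in eligibility windows with a modest and uncertain cost. Criteria 9 and 10 omit the forward window that criteria 1 and 11 have, and the recruitment plan reaches people for whom a planned start is foreseeable.

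On assumed start rates of 10–30% in both arms, weight-loss treatment lowers power from 90.7% to about 89–87%. On assumed rates of 10–20% in the placebo arm, vitamin D lowers it to about 83–72% at worst, and to roughly 88–84% if each starter gains half the effect (87–83% with the added variance). All of this takes the protocol's 0.15 and 0.18 as given. The sample-size arithmetic is correct. The change is worth making because it is cheap and the trial has almost no spare power; the documents do not show that the result would be compromised without it.

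**What to change.** Align the windows in 5.4:

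- Add *or planned in the next 6 months* to criteria 9 and 10.
- Widen criterion 11 from planned bariatric surgery to include a structured weight-loss programme already scheduled to start in the next six months.

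These are entry screens only. They withhold no treatment from anyone and set no rule for care during the trial. No separate restriction on whom to mail in 5.1 is needed, because the criteria do that work at screening.

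The cost is a wording change to three criteria and the loss of some waiting-list candidates; people recruited by any route who have no such plans are unaffected. The change does not catch treatments started after entry that were not planned at screening. The existing medication reports and the weight and 25OHD measurements remain the only check on those.
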